### Proposed primary and secondary outcome measures

The primary outcome of this trial is the number of hospitalizations per patient after one year of study enrollment. Secondary outcomes will be measures of health system utilization at 1-year (reported as all cause and disease specific) and will include the following:Calls to 911 (regardless of whether patient was transported to hospital)Visits to the participating family health team clinics and any after-hours clinicsLength of stay in hospital if admittedMortalityOverall health status assessment using the (Euroqol-5D 3L) EQ-5D-3L measured at baseline and one year after study enrollment [19, 20]Measures of intervention compliance and safety (that is completed assessments and visits and protocol violations identified by physician review of EMR)Cost-effectiveness analysis for this model of care

The family health team electronic patient record data will be linked via the health card number to province-wide administrative health datasets held at the ICES, a section 45 Prescribed Entity under Ontario’s Personal Health Information Protection Act. Health services data at ICES represent ‘transactions’ of health care utilization, such as inpatient/outpatient hospital utilization, emergency room and other ambulatory clinic visits, drug claims for patients 65 and older, claims for physician services in any setting, and others. Linkage to the ICES administrative databases requires use of the Ontario health card number for each subject; following linkage, only the unique ICES encrypted identifier will remain on the files used for analysis. Linkage will allow us to obtain a more comprehensive view of specific health system utilization than could be achieved with unlinked data. Many disease-specific codes have been validated in ICES’ databases [21–23].

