Patients will be asked about health-related quality of life using the EQ-5D-3 L, [20] a validated measure of quality-adjusted life years (QALY). QALY, a preference-based utility measure, incorporates both length of life and quality of life into a single measure. To estimate QALYs, we will convert EQ-5D data collected in the study to utility score using a validated algorithm [19] so no additional data collection will be required. Health-related quality of life assessments will be performed at baseline and 1-year after study enrollment. Assessments will be performed by the community paramedics for patients enrolled in the intervention cohort and by the patients’ primary care physicians in the control cohort.

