The primary outcome, number of hospital admissions over 1 year will be compared by group using both Poisson regression and negative binomial regression analyses. The goodness of fit of both models will be evaluated using Akaike’s information criterion (AIC) statistics. If, in spite of randomization, differences in baseline characteristics are found using bivariate analytical strategies, these variables will be included in the regression model. Multiple imputation algorithms will be developed in order to determine values for any missing data points [30].

The secondary outcome measures, which are largely count measures, will be compared between control and intervention groups using similar Poisson regression and negative binomial models. The proportion of patients who die during the study period will be compared for the intervention and control groups within each disease-specific group using chi-square tests as well as a logistic regression model, adjusting for any potential confounding variables as appropriate.

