### Economic analysis

Subsequent to the outcome analysis, we will conduct an economic analysis. The objective of the economic analysis will be to compare the relative costs and effects of a community paramedicine intervention with usual care. We will conduct the analysis from the perspective of the MOHLTC using data from the randomized controlled trial and ICES. Since the effectiveness outcomes are hospitalization, ED visits, primary care visits, EMS utilization and medication use, which can be expressed in monetary terms (for example, hospitalization cost), we will convert the outcomes to dollars and will analyze the costs of the two groups. Total cost for each patient includes the cost of intervention and the health care costs incurred within 1-year following randomization (as defined in the outcome measures sections). Based on initial intervention assignment, we will analyze the cost variable as a dependent variable to estimate the difference in expected health care cost with a study group as the primary independent variable in a regression model. Employing regression will allow for the adjustment of potential confounders (for example, patient characteristics).

In theory, an ordinary least squares (OLS) model produces unbiased estimates even if the data are skewed; [31] however, additional estimation methods (for example, generalized linear models [32]) and different uncertainty methods (for example, parametric and non-parametric confidence intervals) will facilitate careful investigation of the impact various assumptions have on our conclusions. In addition, we will conduct a cost-effectiveness analysis using mortality and QALY as the outcome of interest. Methods for censored cost and outcome data will be accommodated in a net benefit regression framework [33, 34].

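### Read as written, the count models for secondary outcomes also take in the EQ-5D-3L utility score, whose default Poisson standard error would be several times too large

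*Protocol article*

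**What the plan says.** The protocol article, under Proposed primary and secondary outcome measures, lists overall health status as a secondary outcome, by "EQ-5D-3L measured at baseline and one year after study enrollment". The same section fixes the scale: "we will convert EQ-5D data collected in the study to utility score using a validated algorithm".

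Under Outcome analyses, the secondary outcomes are dealt with as a set: "The secondary outcome measures, which are largely count measures, will be compared between control and intervention groups using similar Poisson regression and negative binomial models". Mortality is given its own methods in the sentence after that, "using chi-square tests as well as a logistic regression model, adjusting for any potential confounding variables as appropriate". The list of secondary outcomes also contains "Cost-effectiveness analysis for this model of care", which the Economic analysis section covers with ordinary least squares and generalized linear models for cost, and with net benefit regression where "we will conduct a cost-effectiveness analysis using mortality and QALY as the outcome of interest".

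The t-tests and Wilcoxon tests under Outcome analyses are stated for baseline characteristics. The article specifies neither a robust nor a scaled variance for the count models.

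**The concern.** A utility score is not a count. Poisson regression takes the variance to be equal to the mean. For a score between 0 and 1 the variance is well below the mean, so the default standard error answers to the noise of an event count and not to the spread of the scores. The plan compares the Poisson and negative binomial fits by Akaike's criterion, but that comparison cannot help, because neither model allows a variance below the mean.

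EQ-5D-3L is the only patient-reported outcome in the list. If it were analysed this way, a modest but real difference in health status would be reported with a confidence interval several times too wide. A null result could then come from the model and not from the data.

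**Working it through.** **The plan's own figure.** The only sample size stated is for the primary outcome: 695 patients (348 per group), rate ratio 0.85, control rate 1.85, over-dispersion 1.0, R-squared 0.05, 80% power, 5% significance level. Tests are stated to be two-sided.

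With V0 = 1/(0.5 × 0.5) = 4 and V1 = 1/0.5 + 1/(0.5 × 0.85) = 4.353:

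N = (1.96 × √4 + 0.842 × √4.353)² / (1.85 × ln(0.85)²) / (1 − 0.05) = 659.3 / 0.95 = 694.0, in agreement with 695.

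The article states no mean, SD, target difference or power for EQ-5D-3L. The EQ-5D inputs below are therefore assumptions: control mean 0.6 to 0.8, SD 0.20 to 0.30, differences 0.05 to 0.20, and all 348 per group scored.

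**Direction of the error.** For a score confined to 0-1 with mean m, the variance is at most m(1 − m), which is below m. The default Poisson standard error is therefore too large whatever the SD. The negative binomial variance is m + αm² with α ≥ 0, so its best fit falls back to Poisson. A fit to simulated utilities gave α of about 0.00002 and the same standard error as Poisson (0.0918).

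**Size of the error.** The ratio of the default Poisson standard error to the true one is about √m / SD:

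- mean 0.60, SD 0.30: 2.58
- mean 0.70, SD 0.25: 3.35
- mean 0.80, SD 0.20: 4.47

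**Worked case: mean 0.70, SD 0.25, difference 0.05.**

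- Linear comparison: SE = 0.25 × √(2/348) = 0.0190, so 0.05/0.0190 = 2.64 and power = Φ(2.64 − 1.96) = 0.75.
- Poisson, default SE: log ratio = ln(0.75/0.70) = 0.0690. Model SE = √(1/(348 × 0.70) + 1/(348 × 0.75)) = 0.0891. True SE = √(0.25²/(348 × 0.70²) + 0.25²/(348 × 0.75²)) = 0.0262. Power = 1 − Φ((1.96 × 0.0891 − 0.0690)/0.0262) = 1 − Φ(4.03), which is below 0.01%.

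**Power over the whole assumed range, 348 per group, two-sided 5%:**

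| Difference | Linear comparison | Poisson, default SE |
|---|---|---|
| 0.05 | 59-91% | at most 0.2% |
| 0.074 | 90-99.8% | at most 2.5% |
| 0.10 | 99% or more | 1-19% |
| 0.15 | about 100% | 68-96% |
| 0.20 | about 100% | above 99% |

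**Check by simulation** (1,000 trials per setting, beta-distributed utilities, mean 0.70, SD 0.25, 348 per group). Rejection rates for differences of 0, 0.05, 0.074, 0.10 and 0.15:

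- t-test: 0.040, 0.756, 0.971, 0.999, 1.000
- Poisson, default SE: 0.000, 0.000, 0.003, 0.066, 0.831
- Negative binomial with dispersion near 0: the same as Poisson
- Poisson, robust SE: 0.040, 0.760, 0.971, 0.999, 1.000

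**Allowing for deaths.** With about 320 scored per group, mean 0.75 and SD 0.22 (also assumed), variance/mean = 0.0484/0.75 = 0.065 and the ratio of standard errors is √0.75/0.22 = 3.9. The smallest difference that reaches significance is about 1.96 × √(2 × 0.75/320) = 0.134.

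**The case against.** The strongest reply is that the sentence qualifies itself: "The secondary outcome measures, which are largely count measures" concedes that some outcomes are not counts. A journal article condenses the plan, and the model for EQ-5D may stand in a fuller document. This has force as to intent. It does not dispose of the point, because the sentence is not silent. It recognises outcomes that are not counts, assigns count models to the whole set, and then makes an exception for mortality but none for health status.

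Second, the power loss depends on an implementation that the article does not fix. With robust standard errors, Poisson power matches the linear comparison. That stands, and the figures above hold only for the default standard error.

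Four stronger readings are tempting, and the article does not support them.

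- A reader might infer that, mortality apart, count models are the only models stated for secondary outcomes. The Economic analysis section gives non-count models for cost and cost-effectiveness, including QALYs derived from EQ-5D. The gap is confined to the comparison of health status itself.
- A reader might infer that the analysis would find no difference regardless of the true effect. At 0.15 the Poisson power is already 68-96%.
- A reader might infer that the plan compares EQ-5D without regard to baseline. It says nothing on EQ-5D covariates, and it provides for adding baseline variables that differ between groups.
- A reader might think of a 0-100 health rating, for which the error could run the other way. The article specifies a utility score and mentions no such rating.

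**Conclusion.** The point holds in a limited form. As written, the between-group comparison of EQ-5D-3L utility falls under models that cannot represent its variance. With default standard errors the test would be severely conservative: under the assumed means and SDs, differences of about 0.05 to 0.07 would almost never be detected, although a linear comparison would have fair to very high power for them. The direction follows from a 0-1 scale alone. The size rests on assumed means, SDs and effects, because the article gives none.

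The primary outcome, its sample size, the mortality comparison and the economic analysis are not affected. The wording should be corrected because a listed outcome is at stake and the remedy is cheap.

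**What to change.** Under Outcome analyses, limit the Poisson and negative binomial models to the count outcomes: 911 calls, clinic visits and days in hospital. Add that one-year EQ-5D-3L utility will be compared by linear regression on treatment group, adjusted for baseline utility and the disease stratum used in randomization, with robust standard errors, and that the adjusted mean difference will be reported with its 95% confidence interval.

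The cost is a sentence or so of wording. No new data are needed, since baseline EQ-5D and the disease stratum are already recorded. Missing baseline scores can be handled by the multiple imputation already planned. If the full analysis plan already names such a model, the article's sentence needs only to be brought into line with it.

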### Recruitment and randomization

Eligible patients will be contacted by their family physician and given multiple opportunities to provide their consent to participate. Enrollment will employ a modified Dillman method [17] with prepaid postage response cards. All patients will be consented using exactly the same process prior to randomization. See Additional files 3 and 4.A block stratified randomization procedure will be used to randomize eligible, consenting patients to treatment or control groups (1:1 ratio). Randomization will occur using a computer generated randomized number sequence allocated by block based on disease, using variable block sizes to avoid substantial imbalances in the number of patients assigned to each group (Figure 1) and to ensure the three disease groups are represented in the intervention or control (usual care) group. Stratification will balance differences in disease characteristics, which may influence the primary outcomes. Should patients have multiple diagnoses, patients with HF will be categorized HF regardless of the other diagnoses and patients with both COPD and DM will be categorized as COPD. Categorization is based on the prevalence of disease previously noted in a subset of patients in which the number of patients diagnosed as having HF was markedly reduced. A preliminary feasibility sample of cases from within the two family health care teams identified 548 patients: 74 COPD patients, 417 DM patients, and 31 HF patients. One patient had all 3 conditions, 17 had diabetes and HF, 1 had HF and COPD and finally 7 patients had both diabetes and COPD. Informed consent will be obtained from all patients prior to enrollment in the EPIC study. Patient recruitment will occur over a 1-year period. Based upon the preliminary feasibility sample and the sample size calculation required to detect a 15% difference in our primary outcome, this will be sufficient time to enroll the required number of patients.

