### Sample size

The proposed sample size is based on yearly hospitalization rates in Ontario of 296/100,000 for HF, [24] 632/100,000 for COPD [25] and 67/100,000 for DM [26] and 1-year mortality rates of 10% for HF, [27] 4.4% for COPD [28] and 8.2% for DM [29]. A Poisson regression with a sample of 695 (348 per group) achieves 80% power at a 0.05 significance level to detect a response rate ratio of at least 0.85 between groups (intervention and control) given a baseline rate of 1.85 and an assumed phi (over-dispersion parameter) of 1.0. The sample size was adjusted since a multiple regression of the covariate of interest on the other covariates in the Poisson regression is expected to have an R-squared of 0.05. We believe this to be sufficient power to detect a clinically relevant improvement of 15% in hospital admission rates. The proposed sample size calculation will be confirmed by using the baseline rates of admission as determined through ICES for patients enrolled in the EPIC study.

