### Outcome analyses

The MITT or efficacy population will consist of all eligible randomized patients who met all eligibility criteria and who received the full study protocol (4 scheduled paramedic visits over a 1-year period or patients randomized to the control group who remained in the study for the full 1-year period). Furthermore, this trial is intended to target patients with chronic disease who are at high-risk for admission to hospital. However, initial patient enrollment into the study was based upon family physician estimation of patient risk; therefore there is a possibility that some patients enrolled in the study do not represent a high-risk group for hospital admission. Patients enrolled in the trial will have their risk of admission assessed based on their actual rates of admission over the previous 3 years. This information will be gathered through linkage with the ICES databases. Cut-off values for low, medium and high-risk categories will be calculated based on a review of the literature and clinical expertise. Only those patients who are determined to be high-risk will be included in the MITT analysis. Conversely, the ITT or effectiveness population includes all patients randomized regardless of their eligibility, adherence to study protocol or calculated risk of admission.

The primary analysis will be done using an ITT analysis. Baseline characteristics of patients in the intervention and control groups within each disease-specific group will be reported using descriptive statistics, mean/SD or median/IQR for continuous variables and count/percent for categorical as appropriate. Tests of significance will be performed using *t*-tests or Wilcoxon rank-sum test for continuous variables and chi-square or Fisher’s exact test (expected counts < 5) for categorical variables as appropriate. Two-sided *P*-value < 0.05 will be used to determine significant differences in baseline characteristics. These analyses are useful not only to assess the comparability of the treatment group but also to describe the sample of subjects who entered the trial. Test of normality for each variable will be determined using the Shapiro-Wilk test *P*-value < 0.05. All tests will be two-sided and carried out at a significance level at 5%.

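### No overall mortality comparison is stated, the disease-by-disease tests are sparse, and length of stay is confined to patients selected after randomisation

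*Protocol article*

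**What the plan says.** **Mortality.** Outcome analyses in the protocol article has the proportion of patients who die "compared for the intervention and control groups within each disease-specific group using chi-square tests", and adds a logistic regression adjusted for possible confounders. The sentence just before it compares the other secondary outcomes simply by arm, so the split by disease is particular to mortality. The preceding paragraph, on baseline characteristics, replaces chi-square with Fisher's "exact test (expected counts < 5) for categorical variables". The mortality sentence has no such switch. On error rates, the plan says "All tests will be two-sided and carried out at a significance level at 5" per cent.

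**Length of stay.** The list of secondary outcomes (Proposed primary and secondary outcome measures) defines length of hospital stay only for those who are admitted. The number of admissions is the primary outcome.

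**Design.** Recruitment and randomization says the trial will "randomize eligible, consenting patients to treatment or control groups (1:1 ratio"), with the sequence "allocated by block based on disease, using variable block sizes". Data analysis and Outcome analyses make intention-to-treat, meaning everyone randomised, the primary population.

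**The concern.** For mortality, a reader of the final report will first ask whether the intervention changed deaths overall. The plan as written answers with three separate tests. Two of them fall in strata that probably hold very few deaths, no correction is made for testing three times, and no rule says how to combine the results. Disease is also absent from the effect modifiers listed under Subgroup analyses, so no test is planned of whether the three results differ.

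For length of stay, restricting the comparison to admitted patients conditions on something that happens after randomisation and that the intervention is meant to change. The admitted patients in the two arms are then no longer comparable groups. If the intervention mainly keeps milder patients out of hospital, those still admitted are sicker on average and stay longer. The outcome can then move the wrong way when the intervention works.

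**Working it through.** **1. The plan's own figure.** Sample size states: "A Poisson regression with a sample of 695 (348 per group) achieves 80% power at a 0.05 significance level to detect a response rate ratio"; the ratio to be detected is 0.85. The other inputs are fixed by "given a baseline rate of 1.85 and an assumed phi (over-dispersion parameter) of 1.0", and the regression of the treatment covariate on the others "is expected to have an R-squared of 0.05". For Poisson regression with a binary covariate split 1:1 (Signorini formula):

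N = [1.960·√4 + 0.8416·√(2 + 2/0.85)]² / (1.85 × (ln 0.85)²) = 659.3; 659.3 / (1 − 0.05) = 694.001, which rounds up to 695.

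The stated size reproduces. It concerns the primary outcome only; no power is stated for mortality or length of stay.

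**2. Strata.** The feasibility sample (Recruitment and randomization) has 548 patients: 31 HF, 74 COPD and 417 diabetes (DM) with a single diagnosis, plus 1 with all three, 17 DM and HF, 1 HF and COPD, and 7 DM and COPD. Under the article's categorisation rule:

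- HF = 31 + 1 + 17 + 1 = 50
- COPD = 74 + 7 = 81
- DM = 417

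**3. Expected deaths at N = 695.** The one-year mortality rates are those in Sample size. That the feasibility mix carries over to the full trial is an assumption. In the last column, the patients per arm are held as shown.

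| Stratum | Patients | Per arm | Mortality | Deaths, total | Deaths per arm | Mortality needed for 5 per arm |
|---|---|---|---|---|---|---|
| HF | 63.4 | 31.7 | 10% | 6.3 | 3.2 | 5/31.7 = 15.8% |
| COPD | 102.7 | 51.4 | 4.4% | 4.5 | 2.3 | 5/51.4 = 9.7% |
| DM | 528.9 | 264.4 | 8.2% | 43.4 | 21.7 | already met |
| All | 695 | 347.5 | 7.8% | 54.2 | 27.1 | already met |

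The pooled rate is (50×0.10 + 81×0.044 + 417×0.082)/548 = 7.8%. At the cited rates, 5 expected deaths per arm would need 5/0.10 = 50 HF patients per arm (100 in all) or 5/0.044 = 114 COPD patients per arm (about 227 in all).

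**4. Power.** Two-proportion normal approximation, two-sided 5%, counting rejections in the expected direction only. The article gives no target for mortality, so the risk ratios are illustrative.

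| Risk ratio | HF | COPD | DM | All randomised |
|---|---|---|---|---|
| 0.85 | 4% | 4% | 8% | 9% |
| 0.70 | 6% | 5% | 20% | 24% |
| 0.50 | 11% | 9% | 50% | 59% |

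For 80% power, the pooled comparison would need about 7,673, 1,773 and 568 patients per arm respectively.

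**5. Multiplicity.** Three independent tests at a nominal 5%: 1 − 0.95³ = 14.3%.

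**6. Length of stay: simulation.** Assumptions:

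- latent severity s is standard normal;
- the control admission rate is 1.85·exp(0.8s − 0.32);
- stay per admission is 7·exp(0.4s) days, the same in both arms;
- the admission rate ratio is 0.85.

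| Measure | Control | Intervention |
|---|---|---|
| Patients admitted at least once | 70.6% | 66.2% |
| Mean stay among admitted patients (days) | 8.46 | 8.57 (8.57/8.46 = +1.3%) |
| Hospital days per randomised patient | 19.4 | 16.4 (16.4/19.4 = −15%) |

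With severity unrelated to admission, the shift vanishes (7.59 in both arms).

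**7. Length of stay: constructed extreme, per admission.** Suppose 85% of control stays average 10 days, 15% are avoidable stays averaging 3 days, and only the latter are prevented. Mean stay goes from 0.85×10 + 0.15×3 = 8.95 to 10.0 days (10/8.95 = +12%), while bed-days fall from 8.95 to 8.5 per control admission (8.5/8.95 = −5%).

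**The case against.** **Mortality has no valid comparison.** A reader might infer this, and the documents do not support it. Allocation is blocked by disease, so each stratum is a randomised comparison and the three together cover everyone.

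**Mortality is certainly compared only by disease.** That is the natural reading, but not the only one: the adjusted logistic model may be meant for the whole trial. The Economic analysis section also uses mortality as an effect measure for intervention against usual care, which presupposes some overall contrast. This stands as a caution. It does not supply a stated overall analysis.

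**Fisher's test is already named.** It appears one paragraph earlier, and repeating it is the kind of detail an article leaves to an analysis plan. That is fair for the choice of test alone. It does not answer the missing overall estimate or the three unadjusted tests, and exact tests would not rescue strata with about 6 and 5 deaths in total.

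**Pooling gains little.** This is true of power: 50% in DM alone against 59% pooled for a halving, and 8% against 9% at a risk ratio of 0.85. The gain is an overall estimate and interval.

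**Stay per admission is a conventional descriptor.** It would be read beside the primary outcome and total costs, both of which cover all randomised patients, so a false signal of harm is unlikely to go unnoticed. The 12% figure is indeed an extreme built by assumption, and a large bias should not be inferred from it. The selection itself remains whatever its size.

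**Conclusion.** The point holds for two secondary outcomes and leaves the primary analysis and its sample size untouched.

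For mortality, the weakness lies in precision, multiplicity and the absence of a stated overall result; the validity of each comparison is not in question. The sparse cells depend on the feasibility mix and the cited mortality rates. Patients chosen as high-risk may die more often, but the HF rate would have to reach about 16% and the COPD rate about 10% before expected deaths reached 5 per arm. The 14% error rate is nominal and assumes each test holds its 5% level, which chi-square may not do with so few deaths.

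For length of stay, the comparison is between groups selected after randomisation. The direction of the bias under a beneficial intervention is plausible, but its size is not known from the documents: nil if severity does not drive admission, about 1% in the simulation, 12% in the extreme case.

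**What to change.** **Mortality.** State that the main analysis is one comparison of all randomised patients, stratified by disease: Mantel-Haenszel, or logistic regression with disease stratum as a covariate. Report an effect estimate with its 95% confidence interval. Give deaths by arm within each disease descriptively, with exact intervals and no separate significance claims. Say plainly that the trial is not powered for modest mortality effects.

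**Length of stay.** Replace the outcome with total days in hospital over the year per randomised patient, zero for those never admitted. Analyse it by arm with a count model that allows over-dispersion, and read it beside mortality because death shortens the time in which days can accrue. Keep stay per admission as a descriptive figure only.

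**Cost.** Wording in the protocol and the analysis plan. The linked administrative records already planned cover inpatient use and death, so no new data, visits or patients are needed.
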